# *Age Nutrition Chirugie* (ANC) study: impact of a geriatric intervention on the screening and management of undernutrition in elderly patients operated on for colon cancer, a stepped wedge controlled trial

**DOI:** 10.1186/s12877-016-0402-3

**Published:** 2017-01-07

**Keywords:** Vulnerable, Nutrition, Cancer, Colorectal tumor, Stepped wedge

## Abstract

**Background:**

Undernutrition prior to major abdominal surgery is frequent and increases morbidity and mortality, especially in older patients. The management of undernutrition reduces postoperative complications. Nutritional management should be a priority in patient care during the preoperative period. However undernutrition is rarely detected and the guidelines are infrequently followed. Preoperative undernutrition screening should allow a better implementation of the guidelines.

**Methods/design:**

The ANC (*“Age Nutrition Chirurgie”*) study is an interventional, comparative, prospective, multicenter, randomized protocol based on the stepped wedge trial design. For the intervention, the surgeon will inform the patient of the establishment of a systematic preoperative geriatric assessment that will allow the preoperative diagnosis of the nutritional status and the implementation of an adjusted nutritional support in accordance with the nutritional guidelines. The primary outcome measure is to determine the impact of the geriatric intervention on the level of perioperative nutritional management, in accordance with the current European guidelines. The implementation of the intervention in the five participating centers will be rolled-out sequentially over six time periods (every six months). Investigators must recommend that all patients aged 70 years or over and who are consulting for a surgery for a colorectal cancer should consider participating in this study.

**Discussion:**

The ANC study is based on an original methodology, the stepped wedge trial design, which is appropriate for evaluating the implementation of a geriatric and nutritional assessment during the perioperative period. We describe the purpose of this geriatric intervention, which is expected to apply the ESPEN and SFNEP recommendations through the establishment of an undernutrition screening and a management program for patients with cancer. This intervention should allow a decrease in patient morbidity and mortality due to undernutrition.

**Trial registration:**

This study is registered in ClinicalTrials.gov NCT02084524 on March 11, 2014 (retrospectively registered).

## Background

Colorectal cancer has the third highest incidence of cancer and the second highest mortality. The incidence and mortality curves significantly increase after the age of 55 years, with patients over 70 years old representing 60.5% of the incidence cases and 75.2% of cancer deaths [1, 2].

While the rates of perioperative morbidity and mortality have been drastically reduced in older patients due to the use of better anesthetic and post-surgical intensive care techniques [3, 4], age remains associated with a decrease in overall survival. The main mortality risk factors have recently been evaluated using a multivaried analysis and this predictive model has been prospectively validated on a test sample population [5]. The authors confirmed that the primary mortality risk factor is age: the risk is 1.8-fold higher between 80 and 85 years while beyond 90 years it is almost 3-fold higher. The increased rate of mortality in older patients compared to younger ones appears to be limited to the early postoperative period, as the disease specific survival ratio after this time is similar to that expected from the age-matched population as a whole [6]. The condition of the perioperative care therefore represents a priority for the improvement of colorectal cancer prognosis in older patients [7–11].

Beyond all the factors that affect the postoperative morbidity and mortality, the nutritional state of the patient is the most important [12]. Undernutrition significantly increases postoperative morbidity-mortality and is responsible for an increase in infectious and non-infectious postoperative complications and in the toxicity linked to the chemotherapy or radiotherapy treatment, leading to a prolongation of patient hospitalization and to an alteration of their quality of life [13].

In the case of colorectal cancer it has been shown that a weight loss greater than 10% prior to surgery [14] and undernutrition [15] are mortality risk factors. Since the rate of undernutrition is high in older hospitalized patients (up to 50%) [16–18], a nutritional assessment with undernutrition screening should be performed systematically before surgery in these subjects. The European guidelines, based on the results of many clinical studies (summary in Fig. 1), recommend undernutrition screening and routine nutritional care before, during, and after cancer surgery [3, 4, 19–27]. However, such guidelines with high levels of evidence are rarely followed [28, 29]. An unpublished pilot study that we have recently carried out showed that, in older patients hospitalized for colorectal cancer surgery, undernutrition was screened in less than 30% of cases and was not exhaustive. Perioperative nutritional care did not conform to the guidelines for over 95% of those patients undergoing endorectal surgery. Such insufficiency in patient screening and care could either be due to a lack of awareness of this health issue, a lack of interest in nutritional measurements by the medical staff, or by a lack of the necessary knowledge and time to rigorously apply the screening and nutritional care. The French geriatric pathway includes the Geriatric Team (GT), whose expertise is to ensure appropriate care and to improve the management of elderly patients. Our hypothesis is that the systematic intervention of the GT will lead to a better knowledge and respect of the perioperative nutritional care recommendations. This intervention will provide training in good practices, improve undernutrition screening in accordance with the guidelines, improve geriatric and nutritional management in surgery departments. It will also help to promote local paramedic referents via repeated training throughout the length of the study. Several training meetings will improve the identification and care of undernourished patients.

**Fig. 1 Fig1:**
[figure not shown]
Recommendations and decision algorithm for the establishment of a nutritional support, according to the current recommendations of the European Society for Clinical Nutrition and Metabolism (ESPEN) and of the French Society of Clinical Nutrition and Metabolism (SFNEP)

**Fig. 2 Fig2:**
[figure not shown]
Schematic representation of the step wedge design of the ANC study: each line represents a center (*n* = 5). Each square represents a time unit (6 months period); white squares: control units (intervention is not yet implemented); blue squares: intervention units (intervention is implemented)

**Fig. 3 Fig3:**
[figure not shown]
Summary of inclusion, non inclusion and exclusion criteria for the ANC study

**Fig. 4 Fig4:**
[figure not shown]
ANC study flow chart

## Methods/design

### Study design

The ANC protocol is an interventional, comparative, prospective, multicenter, randomized protocol based on the stepped wedge trial design [30, 31], which is appropriate for allowing the implementation of a nutritional intervention in older patients by a Geriatric Team (GT) within all participating services. This design involves the sequential rollout of an intervention in centers over several time periods. The order in which the different centers will receive the intervention will be determined at random. The implementation of the intervention in the five participating centers will be rolled-out sequentially over six time periods (every six months), in such a way that each center will initially belong to the “control” arm (without GT intervention) and then to the “intervention” arm (with GT intervention) (Fig. 2). Depending on the center, the pre-intervention phase, as well as the intervention phase, will last from 6 to 30 months. Thus each center will also act as its own control, which will reduce risk of bias and will allow comparison between each support modality (interventional compared to control) and in each group to analyze the effect of time on the effectiveness of an intervention and its learning. The study design will also avoid contamination between patients.

### Setting

The ANC protocol will take place in surgical wards of different French hospitals. Each hospital has its own GT composed of geriatricians and nurses. All the health professionals in the participating surgical wards will be involved in the conduct of the multidisciplinary prevention program (i.e. surgeons, anesthetist, nurses, and nurses assistants).

### Recruitment of patients

Patients eligible for the ANC study will be all subjects over 70 years old admitted for scheduled surgery of a colorectal tumor with or without concomitant metastasis and having given their informed consent to participate in the study. Patients with an emergency hospitalization for colorectal tumor surgery will not be included. (Fig. 3). Patients who are not included will receive the usual care in accordance with the current practices of the unit.

### ANC program

Pre-interventional phaseAn observational phase will precede the GT intervention. During this period, patients meeting the inclusion criteria will be included and followed by the digestive surgery unit in accordance with that unit’s current practices. Five patients will be included in each center per six months period. This phase will allow the usual practices of nutritional care in each surgical unit to be appraised.InterventionThe intervention provided by the GT will consist of a proposed training which will allow the surgical ward health professionals to follow the nutritional care recommendations and participate in the preoperative nutritional screening. Furthermore, the GT will propose, upon request from the surgery unit, a systematic implementation of preoperative geriatric assessment leading to a care in geriatric ward if necessary and the identification and training of local paramedical referents.
***Training of surgical ward staff***
The objective is to teach health professionals in order to follow the recommendations of the French National Health Authority (“Haute Autorité de Santé, HAS”), that are issued from the recommendations concerning perioperative nutritional care [19, 20], through the diffusion of informative documents and the organization of informative meetings.
***Systematic implementation of preoperative geriatric assessment***
A geriatric assessment is planned at least seven days before surgery. It will be performed by the geriatrician of the GT with four objectives:Assess the patient’s history, comorbidities and nutritional status:Nutritional assessment will be performed according HAS recommendation [1]:Notification of a body weight loss ≥5% (10% for severe cases) in one month,And/or Body weight loss ≥10% (15% for severe cases) in six months,Calculation of BMI <21 Kg/m^2^ (18 Kg/m^2^ for severe cases),Results of Albumin <35 g/l (<30 g/l for severe cases),Global Mini Nutritional Assessment (MNA) <17/30.
In addition, each patient will be submitted to a dietetic interview in order to evaluate his daily food intake.Evans criteria for cachexia diagnostic will be recorded, defined by the association of a body weight loss of ≥5% in 12 months (or BMI <20 Kg/m^2^) associated with at least three of the following criteria [32]:Decrease of muscle strength (hand grip strength <20 Kg for women and <30 Kg for men) [33],Analogical Visual Scale (AVS) Fatigue score ≤3 [33],Anorexic syndrome: defined as a decrease in appetite, responsible of a reduction of total calorie intake (<20 Kcal/Kg of body weight/day) or a 2/3 reduction of requested food intake evaluated between 14 and 7 days before surgery or a score ≤23.5 on the anorexic scale (adapted from the questionnaire AC/S12 of FAACT) [34],Decrease of the Lean Mass Index evaluated by the GT between 14 and 7 days before surgery as a calf circumference <31 cm (Mini Nutritional Assessment, MNA; [35]),Abnormal biochemical values (1 of the 3): CRP >5.0 mg/l, hemoglobin <12 g/dl (anemia), Serum-albumin <32 g/l.
and perform a complete clinical examination and a standardized geriatric assessment focusing on:Measurement of weight (Kg) and height (m)Nutritional biologic markers will be systematically collected: albuminemia, pre-albuminemia, C-reactive protein, hemoglobin.Assessment of functional status using the Short Physical Performance Battery (SPPB) [36], the Activity Daily Life (ADL, [37]) and the Instrumental Activity Daily Life (IADL, [38]).Assessment of emotional status using the Geriatric Depression Scale (GDS, [39])Assessment of co-morbidities (CIRS-G test)
propose an adapted preoperative nutritional management according to the nutritional status of the patient using the decision tree for nutritional care [20];advise the surgery team of the nutritional recommendations to follow in the postoperative phase (Fig. 1).

### ANC study schedule

In each surgical department involved in the study, the surgeon will screen all patients for trial eligibility during a preoperative surgical consultation. Patients in the observational period will receive the usual care, in accordance with the current practices of the unit. In the interventional period, the surgeon will inform the patient of a systematic preoperative geriatric assessment.

For the implementation of the intervention, the GT assessment will be standardized for all centers. It will last approximately 90 min and will be carried out by the GT team, together with a dietician, in the surgery or anesthesia unit, depending on the practices of the center. A nutritional management plan, adapted to the nutritional status of the patient, will be prescribed and implemented following this assessment, in accordance with the current recommendations and decision algorithm (Fig. 4).

### Outcome and measurement

The primary outcome measure is to determine the impact of the geriatric intervention on the level of perioperative nutritional management, in accordance with the current European guidelines, of patients aged 70 years old or above who are undergoing surgery for colorectal cancer. This will be accomplished by evaluating the percentage of patients having received a nutritional screening i.e. measurement of body weight and size, calculation of the body mass index (BMI), evaluation of a recent body weight loss and an albumin assay at least 7 days before surgery, and having received oral immunonutrition during 7 days before surgery (if absence of malnutrition) or immunonutrition during 7 days before and 7 days after surgery (if moderate malnutrition) or artificial nutrition during 7–14 days before surgery and 7 days after surgery.

The secondary outcomes are:The percentage of patients having received a nutritional screening, i.e. measurement of body weight and size, calculation of the body mass index (BMI), evaluation of a recent body weight loss and an albumin assay at least 7 days before surgery.The percentage of patients having received oral immuno-nutritionThe percentage of patients with undernutrition, severe undernutrition and cachexiaThe rate and type of postoperative complications, from grade I to V, according to the Common Terminology Criteria for Adverse Events v4.0 (CTCAE) of National Cancer Institute, occurring up to 30 days after surgery.The number of actual oral nutritional supplements intakes with respect to planned ones (noted in the patient diary given at the preoperative geriatric assessment).The comparison of functionality scores obtained on the ADL and IADL, evaluated by the GT between the beginning (between 14 and 7 days before surgery) versus the end (after surgery, the day before or the day of discharge from the surgical ward) of the hospitalization period.The emotional state of the patient evaluated with the mini-GDS (score on 4) and the GDS 15 (if mini GDS score >2).The number of concomitant treatments (number of drug specialties between 0 and 3, between 3 and 6, over 6) during the hospitalization period.

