## Discussion

### Discussion of the study design

The ANC study is based on an original methodology, the stepped wedge trial design which differs from the parallel and cross-over designs and presents several advantages. Due to the type of the intervention, the risk of contamination would have been too high with a one to one randomization, hence the need for clusters. The stepped wedge design may require fewer centers than a parallel group design to ensure similar group comparability [30, 31, 40–42].

This type of study design presents benefits with regard to implementation: the sequential introduction of the intervention in all the centers does not disadvantage any particular center. The implementation will be easier and it can facilitate the organization of the study in routine practice [43].

Moreover, the risk of center bias is minimized because each center is its own control and receives the intervention. Therefore, the impact of the intervention can be estimated from both between and within center comparisons [30, 31, 40, 44].

This design also allows an evaluation of the effects of time period on protocol effectiveness (following the temporal evolution of the application of the recommendations in the centers). Centers will differ in the time spent on the intervention. Centers that switch at the first time period will be more experienced with the ANC intervention than centers that switch at last time period [44].

Finally, the stepped wedge design allows each participating center to benefit from the ANC intervention. This opportunity is a motivational factor for taking part in this study. In accordance with good ethical practice, the intervention is expected to do more good than harm.

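### The only clinical-harm outcome starts at surgery, although a substantial part of the intervention is delivered before it; preoperative harms and patients who never reach surgery are counted in no listed outcome

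*Protocol article*

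**What the plan says.** All references are to the protocol article.

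- **Harm outcome.** Outcome and measurement lists one clinical-harm outcome among the secondary outcomes: the "rate and type of postoperative complications, from grade I to V", graded by CTCAE v4.0 and "occurring up to 30 days after surgery". The wording fixes both the type of event and the window.
- **Start of the intervention.** Under the ANC program, "A geriatric assessment is planned at least seven days before surgery". According to ANC study schedule, the nutritional plan "will be prescribed and implemented following this assessment".
- **Preoperative nutrition.** The primary outcome describes conforming care as "having received oral immunonutrition during 7 days before surgery (if absence of malnutrition"), the same product before and after the operation in moderate malnutrition, or "artificial nutrition during 7–14 days before surgery and 7 days after surgery".
- **Population.** ANC study schedule places eligibility screening at a preoperative surgical consultation. The primary outcome is framed in terms "of patients aged 70 years old or above who are undergoing surgery for colorectal cancer".
- **Analysis.** Statistical analysis compares complications with a Chi-square test between patients who did and did not receive nutritional support.

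**The concern.** Exposure and observation do not line up. The phases differ by design in the days before surgery: intervention patients get the assessment and a nutrition plan, and control patients get the unit's usual care. The harm count opens only once the operation has taken place. A preoperative feeding complication or an unplanned admission while waiting is not a postoperative complication. A patient who dies or is cancelled before surgery cannot have one.

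Two things are at stake. Serious events in part of the pathway that the trial changes would not appear in its outcome tables. And any complication percentage is conditional on reaching surgery, so a difference between phases in who gets that far would go unseen.

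**Working it through.** The plan gives no figure on this point, so there is none to reproduce. Its 84% power concerns the primary outcome and does not enter here.

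**Step 1. Timing, element by element.**

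| Element | Before surgery | After surgery |
|---|---|---|
| Geriatric assessment | 7 days or more ahead | none |
| Immunonutrition, no malnutrition | 7 days | none |
| Immunonutrition, moderate malnutrition | 7 days | 7 days |
| Artificial nutrition | 7 to 14 days | 7 days |
| Complication count | none | to day 30 |

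All three nutrition branches have a preoperative part outside the count. Two also have a postoperative part inside it.

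**Step 2. Does another listed outcome fill the gap?** Supplement intake against plan measures adherence; it may hint at intolerance but records no harm. ADL and IADL change runs from 14 to 7 days before surgery until ward discharge; it may reflect decline, but the second measurement needs an operated patient. Screening, immunonutrition received, nutritional status, mood and number of drugs are not harms. Statistical analysis adds no further harm outcome. None of these records a preoperative adverse event, a death before surgery or a cancellation.

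**Step 3. Number of patients exposed.** With 5 centers, 6 periods and one center crossing at each step, the intervention center-periods number 5 + 4 + 3 + 2 + 1 = 15. At 5 patients each (Sample size), 15 × 5 = 75 intervention patients.

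**Step 4. Bounds on preoperative exposure.**
- Full course in every patient: 75 × 7 = 525 patient-days. The figure 75 × 14 = 1,050 would need everyone to be in the artificial-nutrition branch at its longest.
- Planned 20% conforming care only: 0.20 × 75 = 15 patients, so 15 × 7 = 105 to 15 × 14 = 210 patient-days. Partial courses add an amount the document does not give.
- Calendar share before surgery: 7/(7 + 30) = 18.9% to 14/(14 + 30) = 31.8%. This is a share of days, not of risk.

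**Step 5. Events that could go uncounted.** The rate p below is an assumption. Expected number = 75p; chance of at least one = 1 − (1 − p)^75.

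| p | Expected in 75 | Chance of at least one |
|---|---|---|
| 1% | 0.75 | 53% |
| 2% | 1.5 | 78% |
| 5% | 3.75 | 98% |
| 10% | 7.5 | over 99% |

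Preoperative harms and failures to reach surgery at these rates would not enter the complication outcome.

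**The case against.** The strongest reply is that a journal article condenses a longer protocol. Adverse-event reporting and the handling of non-operated patients may stand there, or in the figures on exclusion criteria and patient flow, which are not shown. This stands as a limit: nobody can say from the article that the trial has no safety reporting. It does not change the outcome and window that are printed, and general safety reporting would not by itself give a comparison between phases.

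Four stronger readings are tempting, and the document does not support them.

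- *The trial could not back its claim of net benefit.* The phrase "the intervention is expected to do more good than harm" is an ethical premise for giving the intervention to every center, not a conclusion to be tested. The primary aim is guideline adherence.
- *A patient converted to emergency surgery drops out of the outcome.* Emergency hospitalizations are barred at inclusion, but the complication window refers to surgery without requiring it to be scheduled. An included patient operated on urgently still has a 30-day window.
- *Up to about a third of the risk, or 1,050 patient-days of exposure, is unobserved.* These figures treat waiting days as equal in risk to days after major surgery, or assume a full course in all 75 patients against a planned 20%.
- *The printed complication comparison between phases is biased.* The printed test compares by support received, not by phase, so widening the window alone would not create a randomised comparison of harm.

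A further objection concerns the remedy. Only intervention patients have the 90-minute assessment, dietetic interview and intake diary, so minor preoperative events would be found more often in that phase. This stands, and it shapes the fix.

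**Conclusion.** The concern holds as a mismatch between a stated outcome window and a stated exposure. Preoperative harms and non-operation are counted in no listed outcome, and the complication comparison is restricted to patients who reached surgery.

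Its size cannot be given. The document contains no preoperative event rate, and the counts above depend on assumed rates of 1% to 10% in 75 patients. The conclusion also takes inclusion to happen at or soon after the surgical consultation, so that an included patient can fail to reach surgery. The postoperative part of the intervention is observed. The primary outcome, a process measure, and its stated power are unaffected. This is a worthwhile correction to a secondary outcome, not a threat to the main result.

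**What to change.** Keep the 30-day postoperative outcome unchanged. Add one separately reported secondary outcome covering all included patients, in both phases, from the surgical consultation to surgery: the number with each serious event that medical files record alike in both phases, namely death, unplanned admission, cancelled or postponed surgery, and conversion to emergency surgery.

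Report these counts by randomised phase (control or intervention). Compare postoperative complications by phase as well, and not only by nutritional support received. With the few events expected, the preoperative comparison will be mainly descriptive.

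The cost is a few CRF lines and a slightly longer chart review. The clinical research assistant already extracts data from the medical files, and Trial status says that data cleaning and analysis had not begun at submission. Some difference in detection between phases will remain. For that reason minor preoperative events should not be pooled with the postoperative outcome. No clinical procedure changes.
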